### Interventions and control

After randomization, patient who are enrolled in this trial will get prepared at the operating rooms in the inpatient centers, with the painful parts of the body exposed. The intervention group will receive the heat-stone massage. The heat-stone massage is a standard procedure: (1) use lubricant on the skin where the patients feel painful; (2) heat the stone to 45–50°C and press the heated stone on the skin and move the stone nearby with pressure for 15 min; (3) massage for 15 min. The patients in the heat-stone massage group will receive the standard procedure 3 times per week for 2 weeks. This heat-stone device and massage procedure has already obtained the utility model patent (No. 18576425). All the heat-stone massage providers have been educated in clinical nursing and have been practicing chronic pain management for at least 5 years. The control group will receive the flurbiprofen plaster on the area where patients feel painful, twice per day for 2 weeks. The standard procedure of heat-stone massage is shown in the Figure 2.

**Figure 2 fig2:**
[figure not shown]
The Standard Procedure of Heat-Stone Massage. **(A)**: heat the stone to 45–50°C; **(B)**: use lubricant on the skin; **(C,D)**: press the heated stone on the skin and move the stone nearby with pressure for 15 min; **(E)**: massage on trapezius, erector spinae, levator scapula, rhomboids major, rhomboids minor for 5 min; **(F)**: massage on trapezius, levator scapula, supraspinatus for 5 min; **(G)**: massage on infraspinatus, teres major, teres minor for 5 min.

### Follow-up visit

The visits will be conducted at the day when patients receive the first treatment, and 7 days, and 14 days after the first treatment, which will be during the intervention duration of 2 weeks. After the end of the intervention, the follow-up visits will be done at day 21, day 28, day 35, and day 42 after the first treatment, which is 1 month follow-up after the intervention.

### Study outcomes and assessment

The primary outcome is the change in the score of Global Pain Scale (GPS, range 0–200, higher scores indicate worse influence on life) from baseline to the end of the 2 week intervention. The GPS is a validated, concise, and easily interpreted score to comprehensively assess the pain, emotions, clinical outcomes, and daily activities (11). The Chinese version of the GPS was also validated in Chinese population (12).

The secondary outcomes include (1) the change in GPS from baseline to the end of 6 week follow-up; (2) the proportion of participants who have clinically significant change in severity of the pain assessed by Numerical Rating Scale (NRS, range 0–10, higher scores indicate worse pain) (13), a change of 20% from baseline to the end of the 2 week intervention is regarded as clinically significant change (14); (3) the change in acceptance of pain assessed by Chronic Pain Acceptance Questionnaire(CPAQ, range 0–120, higher scores indicate higher pain acceptance) from baseline to the end of 2 week intervention (15); (4) the change in health education and self-management assessed by the Health Education Impact Questionnaire (heiQ, range 40–200, higher scores indicate better health self-management) from baseline to the end of 2 week intervention (16); (5) the change in pain-related self-efficacy assessed by the Pain Self-Efficacy Questionnaire (PSEQ, range 0–60, higher scores indicate better confidence of self-efficacy) from baseline to the end of 2 week intervention (17); (6) the change of anxiety and depression assessed by the Hospital Anxiety and Depression Scale (HADS, range 0–42, higher scores indicate more severe symptoms) from baseline to the end of 2 week intervention (18); (7) the change in quality of life assessed by Short Form-36 (SF-36, range 0–100, higher scores indicate better health) from baseline to the end of the 2 week intervention (19).

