Heat-stone massage is using the heated stone to stimulate the muscles, ligaments, and tendons, followed by massage for relaxation. In the framework of Chinese medicine theory, chronic musculoskeletal pain can be regarded as local stagnancy and lack of nourishment in the related meridians; meanwhile, heat can be used to nourish the meridians, stone can be used to stimulate the acupoints to smooth the stagnancy, and massage can relax the local tissue after the heat-stone stimulations to enhance the pain relief. One clinical trial with 56 participants enrolled showed that focal massage with high force significantly lower visual analog scale compared with low force (mean difference of −1.33) (8). Another clinical trial with a total of 78 participants showed that moxibustion-*cum*-massage significantly reduced the pain severity assessed by brief pain inventory compared to control group of no treatment (mean difference of −0.76) (9). Our *unpublished* pilot study showed that heat-stone massage reduced the pain assessed by global pain scale (GPS) by a mean of 4. We hypothesis that this novel heat-stone massage would reduce pain level in patients with chronic musculoskeletal pain. This randomized controlled trial is aimed to investigate the efficacy and safety of heat-stone massage for patients with chronic musculoskeletal pain.

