### Inclusion and exclusion criteria

The inclusion criteria of this trial are (1) chronic primary musculoskeletal pain is clinically diagnosed based on the criteria that chronic primary musculoskeletal pain is chronic pain in the muscles, bones, joints or tendons that is characterized by significant emotional distress such as anxiety, anger/frustration or depressed mood or functional disability such as interference in daily life activities and reduced participation in social roles, including fibromyalgia syndrome which is defined as diffuse pain in at least 4 of 5 body regions which is associated with significant emotional distress or functional disability; (2) chronic musculoskeletal pain symptoms more than 3 months; (3) pain severity of Numerical Rating Scale (NRS) pain score between 4 and 6; (4) pain is often related to weather changes, and symptoms can be aggravated after rainy days and fatigue; (5) age between 18 years and 80 years; (6) volunteer to participate in the trial and sign the informed consent.

The exclusion criteria of this trial are (1) acute pain or chronic secondary musculoskeletal pain or chronic cancer related pain or chronic neuropathic pain; (2) history of cardiovascular and cerebrovascular diseases, liver diseases, kidney diseases, blood system diseases, diabetes, or infectious diseases; (3) history of tuberculosis, rheumatoid arthritis, ankylosing spondylitis, gout, or cancer bone metastasis; (4) history of mental disorders or communication dysfunction; (5) history of peripheral nerve perception disorder; (6) pregnant, lactating women or those who have pregnancy plans; (7) surgical plan in the next 3 months; (8) reported allergy to the interventions in this trial; (9) have used pain killers or received other pain treatment within the last 1 week.

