### Power analysis and sample size calculation

The power analysis and sample size estimation were based on the primary outcome of this trial which is the change in GPS from baseline to the end of the 2 week intervention. One of our pilot studies showed that the mean change in GPS in heat-stone group was 12, while the mean change in GPS in flurbiprofen was 8, with a combined standard deviation of 6.7. With a power of 80%, 2-sided alpha of 0.05, and the assumption that the change is normally distributed, we used the “power twomeans” function in STATA with 1:1 ratio in treatment and control group to get estimated sample size of 46 samples for each group, so that a total of 92 participants are required. Considering the 20% dropout rate, the total sample size of 115 is required. To make it convenient to assign the participants with 2:1:1 ratio to the 3 centers, we took the 120 as the final planned sample size. The sample size was calculated using STATA, version 16.1 (StataCorp, USA).

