### Statistical analysis

The Primary analysis will be conducted on the full dataset of all the participants after randomization based on the intention-to-treat principle. Moreover, sensitivity analysis will be conducted between the full dataset and the per protocol dataset. Participants who are not in the per protocol analysis are nonadherence which might be caused by failure to receive the assigned treatment, suffering from severe adverse events, or loss of follow-up.

To check if there is selection bias and confounding factors, we will compare the baseline characteristics of the two groups. Continuous variables will be described as mean (Standard Deviation) for normal distribution and be tested using t test or be described as median (interquartile range) for skewed distribution and be tested using Mann–Whitney test. Categorical variables will be summarized as counts (percentages) and be tested using Chi squared test or Fisher exact test.

The primary outcome of this trial is the change in Global Pain Scale from baseline to the end of the 2 week intervention. The difference of the changes between the two groups will be analyzed using a generalized linear mixed model. The mean and 95% confidence interval will be calculated and estimated. Known confounding factors that may affect the pain severity in chronic musculoskeletal patients include age, sex, job, duration of the chronic pain, and emotional state. Therefore, we will make the subgroup analysis for the variables of age categories (>60 years vs. ≤60 years), sex (female vs. male), job categories, duration of pain, taking these as covariates in the model.

For the secondary outcomes, generalized linear mixed model will be used for continuous variables, and two proportion z test will be used for proportions, whereas the Chi squared test or Fisher exact test will be used for categorical variables.

The primary economic analysis will be the cost-utility analysis over 6 week using quality-adjusted life years (QALYs) calculated from the SF-36. The mixed-effect linear regression model will be used, adjusting the confounding factors including age, sex, job, and site of recruitment.

All statistical tests will use the statistical significance of 2-sided *p* value of <0.05. All the statistical analysis will be performed using Python, version 3.8.16 (sklearn and statsmodels packages).

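### The NRS responder rule states neither a direction nor 'at least', so read literally worsening by 20% counts as response; define it as a reduction, adjust for baseline, and add a continuous NRS analysis

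*Protocol article*

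**What the plan says.** Under Study outcomes and assessment, secondary outcome (2) is "the proportion of participants who have clinically significant change in severity of the pain assessed by Numerical Rating Scale". The scale is described as "range 0–10, higher scores indicate worse pain". The responder rule follows: "a change of 20% from baseline to the end of the 2 week intervention is regarded as clinically significant change". No other NRS outcome is defined there, although the Abstract lists NRS pain severity first among the secondary outcomes.

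The inclusion criteria require "pain severity of Numerical Rating Scale (NRS) pain score between 4 and 6". Table 1 schedules the NRS before treatment and at days 7, 14 and 42.

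The Statistical analysis section does not repeat or refine the rule. It says that "two proportion z test will be used for proportions", and it plans a generalized linear mixed model for continuous secondary outcomes. No NRS outcome is listed to which that model would apply.

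**The concern.** For the other secondary outcomes, an undirected change does no harm because the sign stays in the data. Once a change is turned into yes or no, the sign is lost unless the rule contains it. This rule does not. On a scale where higher is worse, 5 to 6 is a change of 20%, just as 5 to 4 is.

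The missing 'at least' leaves a second gap. A one-point change from 5 is exactly 20%. It counts under 'at least 20%' but not under 'more than 20%'.

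Two things are at stake. A proportion that mixed benefit with harm could not be read as pain relief, and it would dilute a true difference whenever the worse arm had more worsening. Also, testing a dichotomised score without baseline adjustment, with no continuous NRS analysis beside it, discards information the trial already collects.

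**Working it through.** **The plan's own figure.** The protocol gives no power for the NRS. Its GPS calculation reproduces. With a difference of 12 − 8 = 4, SD 6.7, two-sided alpha 0.05 and power 80%, the two-sample t calculation gives 45.02, so 46 per group and 92 in total. Then 92/(1 − 0.20) = 115, raised to 120. After 20% dropout, 120 × 0.8/2 = 48 per arm, which is used below.

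**What the rule means in points.** Assume whole-number scores, which the documents do not state.

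| Baseline | 20% of baseline | Smallest step of at least 20% | Smallest step of more than 20% |
|---|---|---|---|
| 4 | 0.8 | 1 point | 1 point |
| 5 | 1.0 | 1 point | 2 points |
| 6 | 1.2 | 2 points | 2 points |

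**Effect of direction, simplest form.** Assume 60% vs 40% improve by at least 20%, with 60 per arm.
- Improvement only: difference 20 points, power 0.59.
- Either direction, worsening 5% in both arms: 65% vs 45%, difference still 20 points, power 0.60.
- Either direction, worsening 5% vs 15%: 65% vs 55%, difference 10 points, power 0.20.
- Either direction, worsening 5% vs 25%: 65% vs 65%, difference 0.

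**Effect of direction, three assumed distributions.** Assume baselines 4, 5 and 6 equally likely, normal change rounded to whole points, mean reduction m, SD s, and cut-off k = 1, 1, 2 points.
- Share improving at one baseline: Φ((m − k + 0.5)/s).
- Share worsening: Φ((−m − k + 0.5)/s).
- Both are averaged over the three baselines.
- Power = Φ{[d − 1.96√(2p̄(1 − p̄)/n)] / √([p₁(1 − p₁) + p₂(1 − p₂)]/n)}, with n = 48.

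Worked example (A): m = 1.5 vs 0.5, s = 1.5.
- Massage improving: (0.748 + 0.748 + 0.500)/3 = 0.665. Control: (0.500 + 0.500 + 0.252)/3 = 0.417.
- Massage worsening: (0.091 + 0.091 + 0.023)/3 = 0.068. Control: (0.252 + 0.252 + 0.091)/3 = 0.199.
- Either direction: 0.733 vs 0.616.

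(B) and (C) borrow the pilot's standardised GPS changes, 12/6.7 = 1.79 SD and 8/6.7 = 1.19 SD, and apply them to the NRS. That transfer is an assumption.

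| Case | Worsening | Improvement only | Power | Either direction | Power |
|---|---|---|---|---|---|
| A: reductions 1.5 vs 0.5, SD 1.5 | 7% vs 20% | 67% vs 42% | 69% | 73% vs 62% | 23% |
| B: reductions 2.69 vs 1.79, SD 1.5 | 1% vs 5% | 88% vs 73% | 46% | 89% vs 78% | 33% |
| C: reductions 1.79 vs 1.19, SD 1.0 | 1% vs 3% | 81% vs 63% | 48% | 81% vs 66% | 39% |

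Other approximations move these powers by a point or two.

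**Continuous NRS change.** The standardised difference is 1.0/1.5 = 0.67 in A and 4/6.7 = 0.60 in B and C. At 48 per arm a t test has about 90% and 83% power before scores are rounded. Simulating whole-number scores with baseline adjustment gives about 89%, 81% and 80%, against 46% to 69% for the improvement-only proportion. These figures assume the treatment shifts the whole distribution, which favours the continuous analysis.

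**The case against.** The strongest reply is that the authors plainly mean improvement. They use 'change' without a sign throughout. The pilot is reported as "the mean change in GPS in heat-stone group was 12, while the mean change in GPS in flurbiprofen was 8", on a scale where higher is worse, so the positive numbers must be reductions. The hypothesis is that "heat-stone massage would reduce pain level in patients with chronic musculoskeletal pain". The full protocol or SAP may state the coding. This stands as evidence of intent, and it makes the direction point close to a wording fix. It does not change the article's rule, which fixes scale, threshold and time point but leaves the sign out.

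Three stronger readings are tempting and not supported.

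- *The trial will count worsening as success.* Nothing says so. It is only what the literal wording permits.
- *The 1-versus-2-point step is an error.* It assumes whole-number scoring and 'at least 20%'; with decimals the cut-off runs only from 0.8 to 1.2 points. Any relative threshold varies in points with baseline. Randomisation balances baseline in expectation, so the step does not bias the comparison, and it remains after the rule is corrected.
- *Power collapses to 23%, or the rule could favour the worse arm.* The 23% comes from assuming 20% worsening on an active control against 7% on massage. With pilot-like standardised changes the loss is 9 to 13 percentage points. Reversal would need the gap in worsening to exceed the gap in improvement, which nothing in the documents suggests.

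**Conclusion.** The concern holds in limited form. The stated NRS rule lacks a direction and an 'at least', and no other section supplies them. If worsening were counted, the contrast would be diluted to the extent that worsening differed between arms. The illustrations give power of 69% to 23%, 46% to 33% or 48% to 39%, and essentially no loss if worsening is equal. All rest on assumed NRS means and SDs, whole-number scoring, equally likely baselines and 48 per arm. The documents give no NRS change data, so no single figure can be defended.

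Separately, an unadjusted two-proportion z test as the only defined NRS comparison makes weak use of scores collected at baseline and day 14. That is an avoidable inefficiency rather than a source of bias.

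Severity is minor to moderate, for one secondary outcome.

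**What to change.** - Define response as a reduction in NRS of at least 20% from baseline at day 14. State the score increments used.
- Count worsening as non-response, and report the proportion worsening by at least 20% separately by arm.
- Replace the unadjusted z test with a comparison adjusted for baseline NRS, for example a logistic model reported as an adjusted risk difference with its 95% confidence interval.
- Add NRS change from baseline to day 14 as a continuous outcome, adjusted for baseline, using the mixed model already planned for continuous secondary outcomes.
- Record these changes before unblinded data are analysed.

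The cost is a sentence or two in the outcome and analysis sections and one extra analysis, with no new data or visits. Compared with counting either direction, reported response rates would be somewhat lower: from 73% vs 62% to 67% vs 42% in case A, and from 89% vs 78% to 88% vs 73% in case B.

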### Safety and adverse event reporting

We will monitor the adverse events through the trial, that will be achieved by a research board composed by 1 physician, 1 nurse, and 1 statistician. Because the intervention contains heat therapy and pressure on the skin, empyrosis, bruise, and over sweating are likely to occur during the treatment. Any adverse events related to the study intervention will be reported.

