### Randomization and blinding

All the included participants will be randomly assigned to the heat-stone therapy group (treatment group) or the flurbiprofen plaster group (control group) with a 1:1 ratio with a block size of 6 (R, version 4.2.0). The statistician in our team ([name]) will produce the randomization number list for 3 trial centers, respectively, using central randomization system at the Clinical Assessment Center of China Academy of Chinese Medical Sciences, then randomization list will be automatically sealed in the system including the treatment assignment in it, which will not be seen by any other research staff. This statistician who oversees the randomization will not participate in any process of data collection or outcome analysis. A study nurse in our team ([name]) who is not involved in the randomization number generation or patient recruitment process, will use the randomization sequence in the central randomization system to assign the patients in the outpatient or inpatient centers of the hospital in person. Then the patients will be randomly assigned into the heat-stone massage group or flurbiprofen plaster group. Both the participants and heat-stone massage therapists are aware of the treatment, but the principal investigator of this trial, outcome assessment research staff and data analysis statistician will be blinded to the randomization.

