### Baseline assessment

Baseline visit and assessment will be conducted at the inpatient centers in the hospitals. Demographic information (including sex, age, educational background, job), course of the chronic pain, medical history (including complications, smoking, alcohol), and basic tests (including blood pressure, heart rate), will be collected in person. Baseline assessment about the chronic musculoskeletal pain will include severity of the pain (assessed by Numerical Rating Scale, range 0–10, higher scores indicate worse pain), pain-related overall life assessment (measured by Global Pain Scale, range 0–200, higher scores indicate worse influence on life), acceptance of pain (assessed by Chronic Pain Acceptance Questionnaire, range 0–120, higher scores indicate higher pain acceptance), health education and self-management (assessed by the Health Education Impact Questionnaire, range 40–200, higher scores indicate better health self-management), pain-related self-efficacy (assessed by the Pain Self-Efficacy Questionnaire, range 0–60, higher scores indicate better confidence of self-efficacy), anxiety and depression (assessed by the Hospital Anxiety and Depression Scale, range 0–42, higher scores indicate more severe symptoms), and quality of life (assessed by Short Form-36, range 0–100, higher scores indicate better health). All scheduled visits are shown in the Table 1.

**Table 1 tab1:** The schedule of planned visits.

Study component	Visit 1	Visit 2	Visit 3	Visit 4	Visit 5	Visit 6	Visit 7	Visit 8
Time	1 d before treatment	First treatment	7 ± 1 d after treatment	14 ± 1 d after treatment	21 ± 1 d after treatment	28 ± 1 d after treatment	35 ± 1 d after treatment	42 ± 1 d after treatment
Informed consent	×	–	–	–	–	–	–	–
Demographic	×	–	–	–	–	–	–	–
Pain duration	×	–	–	–	–	–	–	–
Pain locations	×	–	–	–	–	–	–	–
Pain triggers	×	–	–	–	–	–	–	–
Randomization	×	–	–	–	–	–	–	–
Intervention	–	×	×	×	–	–	–	–
NRS	×	–	×	×	–	–	–	×
GPS	×	–	×	×	–	–	–	×
CPAQ	×	–	×	×	–	–	–	×
heiQ	×	–	×	×	–	–	–	×
PSEQ	×	–	×	×	–	–	–	×
HADS	×	–	×	×	–	–	–	×
SF-36	×	–	×	×	–	–	–	×
Pain killer intake	×	–	×	×	–	–	–	×
Adverse events	–	×	×	×	×	×	×	×

NRS, Numerical rating scale; GPS, Global pain scale; CPAQ, Chronic pain acceptance questionnaire; heiQ, Health Education Impact Questionnaire; PSEQ, Pain Self-Efficacy Questionnaire; HADS, Hospital anxiety and depression scale; SF-36, Short Form-36.

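### The article's sole commitment to report adverse events is limited by relatedness, although events are recorded at Visits 2 to 8 without that limit and safety is a stated aim

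*Protocol article*

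**What the plan says.** The Introduction of the protocol article states that the trial is "aimed to investigate the efficacy and safety of heat-stone massage for patients with chronic musculoskeletal pain", and the closing paragraph of the Discussion again promises evidence on both.

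Under Safety and adverse event reporting, a board of one physician, one nurse and one statistician monitors adverse events for the whole trial. The expected events are then named, with heat and skin pressure given as their cause: "empyrosis, bruise, and over sweating are likely to occur during the treatment". None is named for the flurbiprofen plaster. The section ends with its only sentence on reporting: "Any adverse events related to the study intervention will be reported".

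Table 1, under Baseline assessment, has a row "Adverse events" marked at Visits 2 to 8, that is, from first treatment to day 42, with no qualifier.

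Under Randomization and blinding, "Both the participants and heat-stone massage therapists are aware of the treatment", while "the principal investigator of this trial, outcome assessment research staff and data analysis statistician will be blinded to the randomization".

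Under Statistical analysis, the reasons for leaving the per protocol set include "suffering from severe adverse events, or loss of follow-up", again without reference to cause.

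**The concern.** The article collects adverse events on one criterion and commits to reporting them on a narrower one. Between the two stands a causality judgement, for which the article names no judge and states no blinding.

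Such a filter harms a safety comparison when it works differently in the two arms. Two features of the text make that possible. First, the listed expected events all belong to the massage, which may prompt attribution in that arm more than in the other. Second, the sentence just before the reporting rule uses the word intervention for heat and pressure alone, and the article elsewhere contrasts an intervention group with a control group. On that reading, events under the plaster are not covered by the commitment at all.

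At stake is one of the two stated aims. Filtered counts could show a difference that does not exist, hide one that does, or leave an unexpected kind of event out of the results.

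**Working it through.** **The passages side by side**

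| Step | Limited to related events? | Where |
|---|---|---|
| Monitoring by the board | No | Safety and adverse event reporting |
| Recording, Visits 2 to 8 | No | Table 1 |
| Exclusion from the per protocol set for severe events | No | Statistical analysis |
| Reporting | Yes | Safety and adverse event reporting |

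The limit appears only at the last step. One consequence is that a severe event could take a patient out of the per protocol set and still fall outside the reporting commitment.

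**Which arms the rule covers.** Usage is mixed. The safety section and the group labels point to the massage alone. The allergy exclusion uses the plural for both treatments, and the 2-week intervention period in the outcome definitions applies to both arms. The wording does not settle the matter.

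**Size.** The article gives no adverse event figure to reproduce, so only an illustration is possible.

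Inputs:
- From the article: 120 patients at 1:1, so n = 120/2 = 60 per arm.
- Assumed: the same true risk p in both arms (10%, 20% or 30%), and a share a1 or a2 of affected patients whose event is called related.

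Formulas:
- Reported risk in an arm = p × a; expected patients reported = 60 × p × a.
- Reported risk ratio = (p × a1)/(p × a2) = a1/a2, whatever p is.
- Reported risk difference = p × (a1 − a2).
- Chance of p < 0.05 in a two-sided comparison of reported proportions, by normal approximation: Φ{[|p1 − p2| − 1.96·√(2·p̄(1 − p̄)/60)] / √([p1(1 − p1) + p2(1 − p2)]/60)}, where p1 = p·a1, p2 = p·a2 and p̄ is their mean.

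Example with p = 20%, a1 = 80%, a2 = 40%: 12 patients per arm have an event, and 9.6 against 4.8 are reported. p1 = 0.16, p2 = 0.08, p̄ = 0.12. The expression is (0.08 − 1.96 × 0.0593)/0.0589 ≈ −0.62, and Φ ≈ 0.27.

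| Called related, one arm vs the other | Reported patients at p = 20% | Reported risk ratio | Reported risk difference at p = 20% | Chance of a false significant result, p from 10% to 30% |
|---|---|---|---|---|
| 50% vs 50% | 6.0 vs 6.0 | 1.0 | 0 | 5% (nominal) |
| 70% vs 50% | 8.4 vs 6.0 | 1.4 | 4 points | 7% to 13% |
| 80% vs 40% | 9.6 vs 4.8 | 2.0 | 8 points | 15% to 40% |
| 90% vs 30% | 10.8 vs 3.6 | 3.0 | 12 points | 28% to 73% |

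The last column is rough at p = 10%, where expected counts are small (4.8 vs 2.4 in the 80% vs 40% row). It applies only if someone runs such a test; the article plans none.

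The filter can also mask a difference. In general the reported ratio is the true ratio times a1/a2, so an assumed true ratio of 2.0 with shares of 40% and 80% is reported as 2.0 × 0.5 = 1.0. If the rule covers the massage alone, then at p = 20% the plaster arm has 12 affected patients and the commitment requires none of them to be reported.

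**The case against.** The strongest reply is that the text forbids nothing. A reader might infer that unrelated events will be withheld, but the sentence does not say so. Events are monitored and recorded without a limit, and the data section says that all data go to the statisticians, so an all-cause table by arm remains possible. The word reported is not defined either; it could mean notification to the board or the ethics committee and not the results table.

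A reader might also infer that the trial is open-label and that unblinded attribution decides the safety comparison. The documents do not support this. The principal investigator, those who assess outcomes and the analyst are blinded. The person who attributes events is not named, and the board's blinding is not stated. No between-arm safety comparison is specified that attribution could decide. Causality criteria and adverse event tables are commonly left to the full protocol or analysis plan, neither of which is shown, so their absence is no fault.

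Finally, the assumed shares are not evidence: nothing in the article shows that attribution would differ by arm. Patients' knowledge of their arm may also affect which events they mention, and all-cause reporting would not remove that.

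All of this stands, and it limits how strongly the point may be put. It does not remove the point. The article did not leave the reporting criterion to another document; it stated one, and that criterion is narrower than what it collects and ambiguous about the control arm.

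**Conclusion.** The concern holds as a fault in a stated rule. If the sentence is followed as written, a causality judgement of unstated origin and blinding stands between the recorded events and the reported ones, and plaster events may fall outside the commitment. The direction of any distortion is not known. Its size cannot be derived from the article: the reported ratio is undistorted under equal attribution and is multiplied by 1.4 to 3.0 in the unequal scenarios shown, all of which are assumptions. Equal attribution is not wholly harmless either, since it shrinks the absolute risks, and any true risk difference, by the share called related. The primary efficacy analysis is not affected.

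**What to change.** Replace the reporting sentence with a commitment along these lines: all adverse events recorded at Visits 2 to 8 will be reported for both arms, by arm and regardless of attribution, as numbers of patients and of events, including serious events, with relatedness to the assigned treatment shown as an additional column.

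If the full protocol does not already do so, it should add who judges relatedness and whether that person knows the arm. Once relatedness is supplementary, less depends on the answer.

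The cost is one sentence and one table. The events are already scheduled for recording, and no visit, treatment or sample size changes.
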